### Outcome Variables

The main study variables are (1) comparability (eg, is YouthCHAT at least as good or better than HEEADSSS assessment at detecting mental health and lifestyle issues among Year 9 youth? Is it a faster method of screening?), (2) acceptability (eg, is YouthCHAT content/format an acceptable alternative or companion to HEEADSSS assessment?), and (3) utility (eg, is YouthCHAT useful in helping to streamline assessment processes?).

Our primary outcome measures are (1) comparable detection rates for each domain for HEADSSS and YouthCHAT as measured by mental health or lifestyle issue “present” or “absent” (Tamaki sample only), (2) time taken to complete YouthCHAT and HEEADSSS screening (Tamaki sample only), and (3) acceptability and utility of YouthCHAT as assessed via feedback from staff and students/patients (Starship and Tamaki participants). Secondary outcome measures include differences in YouthCHAT versus HEEADSSS screening outcomes by gender and ethnicity.

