YouthCHAT provides summary reports to authorized school/health clinic staff plus a guide to stepped-care management from self-help through to secondary care. It is a rapid screening system (taking 5-15 minutes to complete) and can be conducted on any electronic device. YouthCHAT has a 14-year history of development in primary care, youth, and school clinics [20,21,25-31]. Recently, it was successfully implemented in a rural school clinic and favorably received by both young patients and clinic staff. Evidence indicates that students are more likely to disclose information about challenges they are facing through electronic means than an initial in-person assessment [32].

As a validated and rapid screening tool, YouthCHAT has the potential to overcome barriers associated with HEEADSSS assessment, while providing a similar holistic assessment of mental health and lifestyle issues. Additionally, as YouthCHAT collects and provides electronic data, the additional paperwork that HEEADSSS requires is not needed. YouthCHAT may be a more efficient screener and serve as a useful substitute or precursor to HEEADSSS assessment. YouthCHAT currently screens for all HEEADSSS domains except three: eating issues, conduct problems/bullying, and resilience/strengths. Additional screening questions to cover these domains have been added, based on those available in the existing literature, with appropriate wording advised by high school students, including those of Māori and Pacific Island descent via focus groups to ensure the updated version of YouthCHAT is appropriate for young people from all major ethnic groups in New Zealand.

The aims of this study are to (1) validate three additional YouthCHAT domains against comparable HEEADSSS domains, (2) ascertain the acceptability and utility of YouthCHAT for children with long-term physical illness and high school students, and (3) compare the performance of YouthCHAT and HEEADSSS in the high school setting.

We hypothesize that a version of YouthCHAT matched to HEEADSSS for all domains will be an acceptable alternative to a HEEADSSS assessment to both young people and the clinical staff conducting the screen. We further hypothesize that screening using YouthCHAT, followed up by a targeted or full HEEADSSS assessment where indicated, will be a much more streamlined and efficient system to enable identification and intervention of young people at risk.

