### Measures and Data Collection

#### YouthCHAT

YouthCHAT covers 10 domains: smoking, drinking, recreational drug use, problematic gambling, depression, anxiety, sexual health, exposure to abuse, anger management, and physical activity. In the case of positive screens, branching logic links users to validated assessment tools including SACS for drug and alcohol use, PHQ-9 for depression, and GAD-7 for anxiety. For the purpose of this project, three new domains have been added to YouthCHAT related to diet, body image, and bullying. Questions related to these domains have been developed based on existing validated tools and have been trialled with student focus groups prior to initiation of the study comparing YouthCHAT with HEEADSSS. Interested readers are welcome to contact the authors for the complete list of YouthCHAT questions.

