#### HEEADSSS

HEEADSSS is a clinician-administered, interview-based assessment of youth that can identify mental health and substance use problems [18,19]. It covers the domains of Home, Education/employment, Eating, Activities, Drugs and Alcohol, Sexuality, Suicide/depression, and Safety. It is currently administered by trained school health nurses to all Year 9 students in low-decile schools and some attendees at primary care and pediatric services in New Zealand.

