### Conclusion and Recommendations

If the outcomes indicate that YouthCHAT provides a comparable mental health and psychosocial assessment to HEEADDSSS, is acceptable to young people and clinical staff, and is faster to administer, we propose the following clinical changes.

All Year 9 students in low-decile high schools should be screened using YouthCHAT, and currently routine HEEADSSS assessments should not be undertaken where there is a negative screen. Instead, a tailored (targeted) HEEADSSS assessment should be conducted for the YouthCHAT positive domains.Young people with long-term physical conditions who are admitted to pediatric hospitals or attending routine outpatient clinics for long-term physical conditions should undergo an annual YouthCHAT screen, with targeted HEEADSSS assessment where needed.All students in New Zealand high schools should be screened using YouthCHAT annually.The potential for YouthCHAT to be used in other countries should also be explored.

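### Detection is compared domain by domain, but the proposed change acts on each student, and domain rates do not show how many students would have a HEEADSSS issue no longer asked about

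*Protocol article*

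**What the plan says.** Outcome Variables names three primary outcomes: detection, time taken, and acceptability with utility. Detection is defined as "comparable detection rates for each domain for HEADSSS and YouthCHAT as measured by mental health or lifestyle issue", scored as a yes or no. On the secondary side, "Secondary outcome measures include differences in YouthCHAT versus HEEADSSS screening outcomes by gender and ethnicity". No listed outcome counts students with any discordant domain.

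Conclusion and Recommendations sets the condition for change: "If the outcomes indicate that YouthCHAT provides a comparable mental health and psychosocial assessment to HEEADDSSS, is acceptable to young people and clinical staff". Greater speed is the remaining requirement. Once these are met, the section proposes that "currently routine HEEADSSS assessments should not be undertaken where there is a negative screen"; in its place, it says, "a tailored (targeted) HEEADSSS assessment should be conducted for the YouthCHAT positive domains". The hypothesis in the Introduction is wider: "screening using YouthCHAT, followed up by a targeted or full HEEADSSS assessment where indicated".

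The Procedure section gives every randomised student both tools, in one order or the other. Data Handling says that the YouthCHAT code is copied into the HEEADSSS file so that the two records can be matched.

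**The concern.** The outcome and the conclusion have different units. The outcome is a rate per domain. The proposal decides, for one student at a time, whether there is an interview and what it covers. What a reader needs in order to weigh that proposal is the share of students with at least one HEEADSSS issue in a domain that would go unasked.

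Domain rates cannot supply it. Two tools can have the same rate in a domain and flag different students. Even if the discordant share in every domain were known, the student-level share would still depend on whether the discordances fall on the same students or on different ones. Each domain could therefore look comparable, and the proposal be put forward, without anyone stating how many students it affects, although the trial's own data contain the answer.

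**Working it through.** **The plan's own figure.** There is none on this point. The only power statement (90% with 144 participants) concerns duration, 15 minutes (SD 30) against 45 minutes (SD 90). It contains no detection rate or margin.

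**Inputs.**
- k = 8 HEEADSSS domains, from the HEEADSSS section: "It covers the domains of Home, Education/employment, Eating, Activities, Drugs and Alcohol, Sexuality, Suicide/depression, and Safety".
- YouthCHAT has 10 existing domains ("YouthCHAT covers 10 domains: smoking, drinking, recreational drug use, problematic gambling, depression, anxiety, sexual health, exposure to abuse, anger management, and physical activity") and 3 added ones, so 13.
- m = share of all students who are HEEADSSS-positive and YouthCHAT-negative in a given domain. The documents give no value; 1% and 2% are assumptions, taken as equal across domains.
- Where a split is needed, m = p(1 − s), with p the prevalence of a HEEADSSS issue in a domain and s the share of those that YouthCHAT also flags. p = 10% with s = 90% gives m = 1%; p = 10% with s = 80% gives m = 2%.

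**Step 1: rates do not give m.** If both tools flag 10% of students in a domain, the HEEADSSS-only share can be anything from 0% (same students) to 10% (no overlap).

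**Step 2: m does not give the student-level share.** Under the proposal a discordant domain goes unasked whether the student is negative throughout (no interview) or positive elsewhere (targeted interview). The share affected is therefore the union of the domain discordances. It is at least m (all in the same students) and at most 8m (no overlap). Independent discordances give 1 − (1 − m)^8. An equicorrelated normal latent variable gives intermediate values.

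| m | Minimum | Latent correlation 0.8 | 0.5 | 0.3 | Independent | Maximum |
|---|---|---|---|---|---|---|
| 1% | 1% | 3.6% | 5.7% | 6.8% | 1 − 0.99^8 = 7.7% | 8% |
| 2% | 2% | 6.5% | 10.4% | 12.5% | 1 − 0.98^8 = 14.9% | 16% |

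With no YouthCHAT false positives, the domain rates behind these two rows are 10% against 9% and 10% against 8%.

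**Step 3: separate no interview from a narrower interview.** Assume independence across domains and no false positives. The share of all students who are negative on every YouthCHAT domain yet have a HEEADSSS issue is (1 − ps)^8 − (1 − p)^8.
- p = 10%, s = 90%: 0.91^8 − 0.90^8 = 0.470 − 0.430 = 4.0%. The other 7.7 − 4.0 = 3.7% would have a targeted interview that leaves a domain out.
- p = 10%, s = 80%: 0.92^8 − 0.90^8 = 0.513 − 0.430 = 8.3%. The other 14.9 − 8.3 = 6.6% would have a targeted interview.

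Taken among screen-negative students only, the same counts are 0.040/0.470 = 8.5% and 0.083/0.513 = 16.1%, so the denominator has to be stated.

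**Step 4: precision.** With 144 matched students, the exact 95% CI is about 5 to 16% for 14/144 (about 10%) and about 14 to 28% for 29/144 (about 20%). A proportion among screen-negative students would be less precise, because fewer students enter it.

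**The case against.** **It could be left to an analysis plan.** The data are paired and matched, the protocol's list of analyses is not closed, and Outcome Variables first asks broadly whether YouthCHAT detects issues as well as HEEADSSS. A reader might infer that the protocol rules out a student-level analysis. It does not. What stands is that the protocol itself fixes the detection outcome per domain and itself draws a per-student proposal from the results; an unseen plan does not change either statement.

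**HEEADSSS is not the truth.** The Introduction calls it unvalidated and dependent on the assessor, and says that young people disclose more electronically. The Discussion says there is no other gold standard. This stands in full. A discordant domain is not shown to be a missed problem, and a count in one direction only would report losses without gains.

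**The sizes are assumed.** This also stands. Independence lies almost at the ceiling of the possible range, and positive correlation between domains, which is plausible, lowers the total.

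**The recommendation is a conditional discussion proposal.** It also rests on acceptability and speed, it includes annual screening for some groups, and the Introduction allows a full interview where indicated. All of this softens the consequence. None of it supplies the student-level figure, and the two descriptions of the follow-up interview do not agree with each other.

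**Conclusion.** The point holds as a mismatch between the unit of the detection outcome and the unit of the proposed change. With eight domains, per-domain discordance of m is compatible with m to 8m of students having a HEEADSSS-identified issue that would no longer be asked about: 1 to 8% at m = 1% and 2 to 16% at m = 2%. These figures rest on an assumed m that is equal across domains. The 4.0% and 8.3% with no interview at all rest further on 10% prevalence, independence and no false positives.

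A reader might infer that the change would leave 8 to 15% of students without an interview they needed. The documents do not support that. They give no per-domain loss and no correlation, part of the total would still have a targeted interview, and HEEADSSS is no reference standard. The trial remains valid; what is missing is a number that its main recommendation depends on.

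**What to change.** State in advance how the 13 YouthCHAT domains map to the 8 HEEADSSS domains. Several YouthCHAT domains may feed one HEEADSSS domain (smoking, drinking and drug use, for instance), so a negative HEEADSSS-equivalent domain has to be defined. Then, from the matched records, add to the first primary outcome, each with a 95% CI and its denominator:

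- (a) among students negative on all YouthCHAT domains, the share with at least one HEEADSSS issue;
- (b) among all students, the share with at least one HEEADSSS-positive, YouthCHAT-negative domain;
- (c) among all students, the reverse share, with at least one YouthCHAT-positive, HEEADSSS-negative domain.

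Say in Conclusion and Recommendations that the proposal is to be read against these figures and not against the domain rates alone. Reconcile that section with the Introduction on the scope of the follow-up interview.

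The cost is the mapping and some extra tabulation, with no new participants or procedures. The published figures may look less favourable than the domain rates.

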#### Administrative Data

Administrative data such as staff time to complete screening/assessments, psychosocial issues identified via HEEADSSS and YouthCHAT, and referrals made based on positive screens will be collected.

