Any focus group participants at the tertiary pediatric hospital who are distressed or develop psychosocial concerns during or following the study will be referred to the hospital-based consult liaison (mental health) service for further assessment and management, in a similar manner to what would occur as part of usual care. Within the high school setting, stepped-care resources and a clinical pathway (algorithms relating to domain and severity of identified problem) will be provided to augment usual care options. These include self-help resources (helplines, psychoeducation and information sheets, websites, and e-therapies), clinician interventions (medications and brief interventions), local community agencies, and referral to adolescent secondary care mental health and drug and alcohol services.

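### Equal per-domain detection rates do not show how many students only HEEADSSS flagged, or how many of those were referred, yet they are to support dropping routine HEEADSSS after a negative YouthCHAT

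*Protocol article*

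**What the plan says.** Under Outcome Variables, the first primary outcome is that detection rates in each domain are comparable between the two tools, "as measured by mental health or lifestyle issue" present or absent, in the school sample only. The question behind it is "is YouthCHAT at least as good or better than HEEADSSS assessment at detecting mental health and lifestyle issues among Year 9 youth". On secondary outcomes the article says: "Secondary outcome measures include differences in YouthCHAT versus HEEADSSS screening outcomes by gender and ethnicity". Neither referral nor severity is named in an outcome, and utility is assessed through feedback from staff and young people.

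Other sections plan data that bear on action:

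- Administrative Data: psychosocial issues found by each tool are recorded, and "referrals made based on positive screens will be collected".
- YouthCHAT (under Measures and Data Collection): after a positive screen, "branching logic links users to validated assessment tools including SACS for drug and alcohol use, PHQ-9 for depression, and GAD-7 for anxiety".
- Procedure: the school receives a clinical pathway with "algorithms relating to domain and severity of identified problem".
- Data Handling: a unique YouthCHAT code goes into each student's HEEADSSS file so that the two can be matched.

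Conclusion and Recommendations then says that, if YouthCHAT is comparable, acceptable and faster, "currently routine HEEADSSS assessments should not be undertaken where there is a negative screen". Domains positive on YouthCHAT would get a targeted HEEADSSS.

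**The concern.** The proposal changes what happens to one group: students whom HEEADSSS flags in a domain and YouthCHAT does not. A comparison of two rates does not count that group. It shows only whether the number flagged by HEEADSSS alone is about equal to the number flagged by YouthCHAT alone. It also says nothing about whether staff acted on what HEEADSSS alone had found.

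So a finding of comparable rates could be carried into the recommendation without anyone having looked at the students it affects, although both tools, the referrals and the student-level link are in the planned data.

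**Working it through.** **Nothing to reproduce.** The article gives no figure for detection or referral. Its one power statement (144 participants, 90%) concerns duration. Only the 144 is borrowed here.

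**Step 1: what a rate difference contains.** For one domain and N students, let a = positive on both tools, b = HEEADSSS only, c = YouthCHAT only, d = negative on both.

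- HEEADSSS rate = (a + b)/N
- YouthCHAT rate = (a + c)/N
- Difference (YouthCHAT minus HEEADSSS) = (c − b)/N

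The difference depends only on c − b. It is 0 whenever b = c, whatever the size of b.

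**Step 2: an illustration.** Inputs:

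- N = 144 (Power Calculation and Data Analysis).
- About 27% positive on each tool: 0.27 × 144 = 38.9, taken as 39. The 27% is the Introduction's figure for anxiety and depression; applying it to one domain is an assumption.
- b = c = 10: assumed.
- 14 students referred in the domain: assumed, about 10% of 144 (14.4).

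| | YouthCHAT + | YouthCHAT − | Total |
|---|---|---|---|
| HEEADSSS + | 29 | 10 | 39 |
| HEEADSSS − | 10 | 95 | 105 |
| Total | 39 | 105 | 144 |

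Both rates are 39/144 = 27.1% and the difference is 0. The paired table alone shows what the rates hide: YouthCHAT was negative in 10 of 39 HEEADSSS positives (26%). No severity information is needed for that.

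**Step 3: what referral adds.** The paired table does not say which of the 10 were acted on. With 14 referred in the domain, the HEEADSSS-only cell can hold between 0 and 10 of them: 0/14 = 0% to 10/14 = 71%. The two rates, and the table itself, are identical throughout.

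**Step 4: the same result another way.** Suppose 8 of the 39 HEEADSSS positives are at referral level (assumed). If YouthCHAT misses m of these and flags m other students, both rates stay at 27.1%. For m = 0, 4 and 8, YouthCHAT finds 8/8 = 100%, 4/8 = 50% and 0/8 = 0% of them.

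**Step 5: precision.** If none of k referred students was YouthCHAT-negative, the exact two-sided 95% upper limit for the proportion is 1 − 0.025^(1/k).

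| Share of 144 referred (assumed) | k | Upper limit for 0/k |
|---|---|---|
| 5% | 7 | 41% |
| 10% | 14 | 23% |
| 20% | 29 | 12% |

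For 3 of 14 (21%), the exact 95% interval is 4.7% to 50.8%.

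**The case against.** A present/absent result per domain is a normal endpoint for a screener, and the article states nothing false about it. The matching code suggests that a student-level comparison may be intended, and how linked data are tabulated is commonly left to an analysis plan. The secondary list is also worded as open. This stands as far as the tables go: their absence from the article is not the fault. What remains is that the article itself states both the outcome and the recommendation to be drawn from it, and the stated conditions for the recommendation do not include the students it affects. The recommendation is a conditional proposal in the Discussion, not a prespecified decision rule, which limits the weight of the point but does not remove it.

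A reader might go further and infer that the primary outcome is unsound because it counts a trivial miss like a serious one, and that up to 71% of referrals would be lost. The documents do not support this:

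- Nothing in the article calls any positive result trivial, or any YouthCHAT-only positive harmless. Results are per domain, so a serious domain is never pooled with a minor one.
- The zero difference in Step 2 comes mainly from comparing marginal rates, not from ignoring severity.
- A student negative in one domain but positive in another would still have a targeted HEEADSSS. The domains also do not map one to one: YouthCHAT separates depression and anxiety, while HEEADSSS lists one suicide/depression domain. A referral in a YouthCHAT-negative domain is therefore not necessarily lost.
- Referral is not an independent measure of need. Staff can read the YouthCHAT reports, every student has both tools, and the Introduction describes HEEADSSS as unvalidated and dependent on the assessor.

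**Conclusion.** The point holds in a limited form. Equal per-domain detection rates cannot by themselves support withholding routine HEEADSSS after a negative YouthCHAT, because they do not give the number of HEEADSSS-only students or the number of those referred. That is algebra and needs no assumption.

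The size is not known from the article. The 0% to 71% range rests wholly on assumed inputs (10 discordant each way, 14 referred) and marks a worst case. The sample also cannot settle the matter: with 7 to 29 referred students, even no misses leaves an upper limit of 41% to 12%. The added result would be descriptive and would limit what can be concluded. A pass/fail rule on one proportion is not warranted, since no threshold is available and referral is an imperfect marker of need. The trial remains valid; this is a worthwhile addition that uses data largely planned already.

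**What to change.** 1. For each domain that can be mapped between the tools, report the paired 2x2 table and the number of students referred within each cell. Give the proportion of referred students who were YouthCHAT-negative in that domain with an exact 95% interval. Record the domain of each referral if this is not already done.
2. Report the number of students negative on every YouthCHAT domain who were referred. These are the students who would have no targeted HEEADSSS under the proposal.
3. For YouthCHAT-only positives, give severity bands only where a graded scale exists; the article names SACS, PHQ-9 and GAD-7.
4. Describe referral as an imperfect marker of need, because staff may see both tools and HEEADSSS is unvalidated.
5. State in Conclusion and Recommendations that the first proposal will be read together with this result and its interval, not on equal detection rates alone.

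Cost: at most one extra field on the referral record, one cross-tabulation per mapped domain and a sentence of text, with no added burden on students. Analysis is planned for the end of 2017, so the tables can be specified before results are seen. The drawback is real: counts per domain will be small and the intervals wide.

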### Participants and Recruitment

During the first phase, up to 20 senior students aged 16-18 years from Tamaki College, a low-decile high school in Auckland, New Zealand, were invited to participate in focus groups to update YouthCHAT via flyers sent to their school. These students were chosen as they were all able to give their own consent.

During the second phase, approximately 150 Year 9 students (aged 13-14 years) from the same high school will be invited to participate in the RCT and school-based acceptability evaluation via letters will be sent to their parents. Parents may use a reply-paid form to opt out of the study if they do not wish their children to participate. However, regardless of this, all students will receive mandatory HEEADSSS assessments (as is routine for all students in this class). Students who choose to participate in the study will be randomly assigned to one of the two conditions (YouthCHAT followed by HEEADSSS assessment or HEEADSSS assessment followed by YouthCHAT) via a computer-generated random numbers table, with resulting lists provided to clinic staff. Sampling will be consecutive until all enrolled students have completed assessment. All screening will take place in the student health clinic on a desktop computer. A subset of 32 students will be invited to participate in four focus groups, and four school staff (nurses and counsellors) will be invited to complete semistructured interviews on the acceptability, utility, and comparability of YouthCHAT and HEEADSSS assessment. This age group of participants was chosen as it matches the age group of students who routinely receive HEEADSSS assessments in New Zealand low-decile schools.

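### Utility is defined as streamlining but measured by feedback; no stated outcome uses the randomised order to estimate what a preceding YouthCHAT does to HEEADSSS interview time

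*Protocol article*

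**What the plan says.** All references are to the protocol article.

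- **The question.** Outcome Variables lists as the third main study variable "utility (eg, is YouthCHAT useful in helping to streamline assessment processes". The Introduction carries the same idea as a hypothesis: "screening using YouthCHAT, followed up by a targeted or full HEEADSSS assessment where indicated, will be a much more streamlined and efficient system".
- **The measure.** The third primary outcome is "acceptability and utility of YouthCHAT as assessed via feedback from staff and students/patients".
- **The time outcome.** The second primary outcome is "time taken to complete YouthCHAT and HEEADSSS screening (Tamaki sample only"). Outcome Variables puts the question of speed under comparability, not utility.
- **Other objective data.** The Administrative Data section opens with "Administrative data such as staff time to complete screening/assessments" and adds issues identified and referrals made.
- **The randomisation.** Participants and Recruitment states: "Students who choose to participate in the study will be randomly assigned to one of the two conditions". The conditions differ only in order, and HEEADSSS is mandatory for every student.
- **The stated comparisons.** Procedure compares the findings of the two tools. Power Calculation and Data Analysis powers a difference in duration between the two tools. The secondary outcomes are tool differences by gender and ethnicity. None of these is a comparison between conditions.

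**The concern.** Streamlining is a statement about process: what happens to the assessment when YouthCHAT is placed in front of it. The outcome that carries this question is assessed by perception. The time outcome does not fill the gap. The article already describes YouthCHAT as taking 5 to 15 minutes and HEEADSSS up to 45, and showing that a self-completed screener is shorter than an interview says nothing about the interview that follows it. A preceding YouthCHAT could shorten that interview, leave it unchanged, or lengthen it by raising more to discuss.

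Students each experience only one order, so their feedback cannot readily separate these possibilities. School staff see both orders, but four are to be interviewed. The randomised comparison of HEEADSSS time between conditions addresses the question directly and needs no new data. At stake is whether the trial can put an objective estimate beside the opinions when it reports on YouthCHAT as a precursor or companion to HEEADSSS.

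**Working it through.** **The plan's own figure.** The article gives 90% power with 144 participants for mean durations of 15 minutes (SD 30) and 45 minutes (SD 90), a difference of 30. At two-sided 0.05 (alpha is not stated):

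- As two independent groups of 72: SE = sqrt(30²/72 + 90²/72) = sqrt(125) = 11.18; 30/11.18 = 2.683; power = Φ(2.683 − 1.960) = 76.5%.
- As 144 pairs with zero correlation: SE = sqrt((30² + 90²)/144) = 7.91; 30/7.91 = 3.795; power = Φ(3.795 − 1.960) = 96.7%.

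Neither gives 90%. That is a separate matter. What counts here is that the calculation concerns tool against tool, so it gives no power for a comparison of conditions.

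**The between-condition contrast.** Inputs:

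- 75 students per condition. This assumes that all of the roughly 150 take part and that allocation is 1:1, which the article does not state.
- Two-sided alpha of 0.05 (assumed).
- HEEADSSS SD: 10 to 15 minutes is an assumption. 22.5 is half the range of 0 to 45, the largest SD possible if no interview exceeds the 45 minutes given in the Introduction. 90 is the article's only stated HEEADSSS SD.

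Formulas, with sqrt(2/75) = 0.1633:

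- Detectable difference = (1.960 + z_power) × SD × 0.1633, where z_power is 0.842 for 80% and 1.282 for 90%.
- Half-width of the 95% interval = 1.960 × SD × 0.1633.

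| HEEADSSS SD (min) | Detectable, 80% power | Detectable, 90% power | 95% CI half-width |
|---|---|---|---|
| 10 (assumed) | 4.6 | 5.3 | 3.2 |
| 15 (assumed) | 6.9 | 7.9 | 4.8 |
| 22.5 (ceiling for 0–45) | 10.3 | 11.9 | 7.2 |
| 90 (Power Calculation) | 41.2 | 47.6 | 28.8 |

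With 72 per condition the 90% figures become 5.4, 8.1, 12.2 and 48.6.

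At an SD of 90 the detectable difference exceeds the assumed HEEADSSS mean of 45. With 72 per condition, power is then about 10% for a 10-minute saving, 17% for 15 minutes and 27% for 20 minutes. However, an SD of 90 cannot hold together with interviews of at most 45 minutes, for which 22.5 is the ceiling. The article does not settle which is nearer the truth.

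**The case against.** The strongest reply is that efficiency already has objective data. Completion time for both tools is a primary outcome, and staff time and referrals are recorded. A reader might infer that streamlining is measured by opinion alone, and the documents do not support that. What is missing is a link from the times to utility and to the randomised condition. HEEADSSS time itself is inside the second primary outcome; only its comparison between conditions is unnamed.

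Nor does the feedback come from a handful of people. About 150 students and 30 hospital patients are to complete a survey covering utility, 32 students are invited to focus groups, and 10 to 15 clinicians are to be interviewed across the settings. And this is not the only contrast that the randomisation allows: YouthCHAT time, and detection by either tool, can equally be compared by condition.

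The most substantial objection is scope. The hypothesis concerns a targeted or full HEEADSSS where indicated, and the Conclusion and Recommendations place the saving in omitting or targeting the interview. Here every student has the mandatory HEEADSSS and no arm is described as targeted. The contrast therefore cannot stand as the measure of utility, and the feedback should not be demoted in its favour. The article also does not say whether the nurse reads the YouthCHAT report before the interview. If not, the contrast says little about streamlining.

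These objections stand and limit the point. The remaining one, that analysis by order may be in a full protocol or SAP not shown, stands only for the analysis model. The measure of utility is fixed in Outcome Variables.

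**Conclusion.** The point holds in a limited form. The outcome that asks about streamlining is measured by feedback, the times collected are set to compare the two tools with each other, and no stated outcome uses the randomised order to estimate the effect of a preceding YouthCHAT on HEEADSSS time. This is a missed use of data the trial will already hold. It does not invalidate the planned comparisons.

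The value of the contrast rests on the true SD of HEEADSSS time. It is useful if interviews stay within about 45 minutes (detectable difference at most about 12 minutes with 90% power and 75 per condition) and uninformative at an SD of 90 (about 48 minutes). It therefore belongs as a supporting estimate with a confidence interval. It answers what happens when YouthCHAT precedes a full HEEADSSS, and nothing more.

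**What to change.** In Outcome Variables, add a secondary outcome supporting utility: HEEADSSS staff time by randomised condition, Condition 1 minus Condition 2, reported as a mean difference with a 95% confidence interval. Keep the feedback alongside it.

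State three things with it:

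1. It tests YouthCHAT before a full HEEADSSS, not the targeted pathway.
2. Whether interviewers see the YouthCHAT report before the interview. If they do not, the contrast serves only as a check for an order effect.
3. The SD expected for HEEADSSS time, so that readers know what precision to expect.

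The cost is one extra analysis of times already recorded and one more reported outcome. It needs no additional students, visits or staff.
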